# Design of the Park-in-Shape study: a phase II double blind randomized controlled trial evaluating the effects of exercise on motor and non-motor symptoms in Parkinson’s disease

**DOI:** 10.1186/s12883-015-0312-6

**Published:** 2015-04-16

**Keywords:** Parkinson disease, Physical activity, Exergaming, RCT

## Abstract

**Background:**

Parkinson’s disease (PD) is a neurodegenerative disorder with a wide range of motor and non-motor symptoms. Despite optimal medical management, PD still results in a high disability rate and secondary complications and many patients lead a sedentary lifestyle, which in turn is also associated with a higher co-morbidity and mortality. Exercise has been explored as a strategy to reduce secondary complications and results suggests that it not only provides general health benefits, but may also provide symptomatic relief. If this holds true exercise would be a very attractive addition to the therapeutic arsenal in PD. The supportive evidence remains incomplete. Here, we describe the design of the Park-in-Shape study, which primarily aims to evaluate whether aerobic exercise affords clinically relevant improvements in motor symptoms in sedentary PD patients. A specific new element is the introduction of gaming to optimize compliance to the exercise intervention.

**Methods/Design:**

The Park-in-Shape study is a randomized controlled, assessor- and patient-blinded single center study. Two parallel groups will include a total of 130 patients, receiving either aerobic exercise on a home trainer equipped with gaming elements (“exergaming”), or a non-aerobic intervention (stretching, flexibility and relaxation exercises). Both groups are supported by a specifically designed motivational app that uses gaming elements to stimulate patients to exercise and rewards them after having completed the exercise. Both interventions are delivered at home at least 3 times a week for 30–45 minutes during 6 months. Eligible patients are community-dwelling, sedentary patients diagnosed with mild-moderate PD. The primary outcome is the MDS-UPDRS motor score (tested in the *off state*) after 6 months. Secondary outcomes include various motor and non-motor symptoms, quality of life, physical fitness, and adherence.

**Discussion:**

This Park-in-Shape study is anticipated to answer the question whether high intensity aerobic exercise combined with gaming elements (“exergaming”) provides symptomatic relief in PD. Strong elements include the double-blinded randomized controlled trial design, the MDS-UPDRS as valid primary outcome, the large sample size and unique combination of home-based pure aerobic exercise combined with gaming elements and motivational aspects.

**Trial registration:**

Dutch trial register NTR4743

## Background

Despite optimal medical management, Parkinson’s disease (PD) remains a disabling and costly neurodegenerative disease in current clinical practice. The disease-related motor and non-motor symptoms largely determine the patients’ disability and therefore their quality of life. In addition many PD patients lead a sedentary lifestyle due to these symptoms, resulting in a higher co-morbidity and mortality. Additional strategies that reduce these symptoms as well as their secondary complications are needed to expand the patients’ functional ability, optimize independence and improve quality of life. Over the last decades exercise has been explored as such a strategy and has shown promising results, with positive effects on generic health benefits as well as on disease-related symptoms [1-3]. Studies in animal models of PD have demonstrated that high-intensity exercise can provide symptomatic relief of parkinsonian signs [4]. Similar results were seen in small treadmill studies in PD patients, showing improvement in gait parameters and enhanced physical fitness [5-7]. Perhaps even more fascinating are the observed changes in the “parkinsonian” rodent striatum after aerobic exercise, including: (a) increased angiogenesis [8], (b) decreased expression of brain damage markers [9], (c) decreased expression of the dopamine active transporter, (d) increased D2 receptor mRNA levels and even (e) reversal of dopaminergic cell loss [4,10,11]. Two recent small cohort studies in PD patients show similar results following high-intensive aerobic exercise. Specifically, postsynaptic D2 receptor binding potential on PET imaging increased [12] and cortical hyperexcitability (which is characteristic for the parkinsonian state), as measured with transcranial magnetic stimulation, reduced [13]. This suggests that intensive aerobic exercise may promote adaptive plasticity of the dopaminergic system, raising hopes that exercise might change the course of PD. If this holds true, exercise would be a very attractive addition to the therapeutic arsenal in PD.

Based on these promising results, (aerobic) exercise is already widely advocated as symptomatic treatment in current practice. However, the strength of the available evidence remains limited, due to small sample sizes and the uncontrolled or non-randomized nature of previous research. In addition, heterogeneous interventions (type, intensity and duration) and outcomes were used, making a meta-analysis or systematic review challenging [2,3,14,15]. Finally, treatment compliance is major challenge in any exercise study, particularly if the exercise should be maintained for long periods (up to many years) to achieve full benefits.

Here, we describe the design of the Park-in-Shape study, a controlled, assessor and patient-blinded single centre study that addresses some of the aforementioned shortcomings. A specific new element is the introduction of gaming to optimize compliance to the exercise intervention, in three different ways: to motivate patients to *begin* the exercise; to stimulate patients *during* the actual exercise; and to reward patients *after* having completed the exercise.

### Objectives

The primary objective of the Park-in-Shape study is to evaluate whether aerobic exercise can lead to clinically relevant improvements in motor functioning in sedentary PD patients. The secondary objectives are to evaluate whether aerobic exercise results in improvements in other clinically relevant symptoms, physical fitness and quality of life.

## Methods/Design

### Ethical approval and trial registration

The study is executed in compliance with the Helsinki Declaration. The study protocol, patient information and informed consent forms have been approved by the local ethics committee (CMO Arnhem-Nijmegen; NL47747.091.14.). Informed consent is signed at the beginning of the in-person assessments, after the patient is fully informed about the procedures. The Park-in-Shape trial is registered in the Dutch trial registry (www.trialregister.nl registration number NTR4743).

### Study design

The Park-in-Shape study is a randomized controlled, double-blinded study performed in a single center (Figure 1). Patients are randomly assigned to the intervention (aerobic exercise) or the active control group (stretching), but are unaware of the allocation possibilities. The assessors performing the baseline and follow-up assessments (directly after the intervention period of 6 months) are also blinded for allocation. Motivational aspects are applied in both groups to increase compliance (see below for further details).

**Figure 1 Fig1:**
[figure not shown]
Study designPark-in-shape.

### Study population

In- and exclusion criteria are shown in Table 1. Included participants are community-dwelling patients with a sedentary lifestyle. All patients who performed none or insufficient aerobic physical activity according to the current recommendations for of the American College of Sports Medicine (ACSM) for older adults [16] (i.e. vigorous exercise performed < 3 times a week, 20 minutes per session or moderate exercise performed <5 times a week, 30 minutes per session) are considered to have a sedentary lifestyle and are eligible. Furthermore, eligible patients are aged between 30 and 75, have idiopathic PD diagnosed by a neurologist (using the UK Brain Bank Criteria), with Hoehn and Yahr stages I-II (tested in the *off* state) [17,18]. Both medicated and unmedicated patients are eligible. Medicated patients can only be included if they receive a stable dopaminergic medication dose for at least one month prior to inclusion in the study (levodopa and/or a dopamine agonist are allowed). Unmedicated patients are eligible if they are deemed unlikely to start treatment within the next month, as judged by their treating neurologist.

**Table 1 Tab1:** **In- and exclusion criteria**

Inclusion criteria	Exclusion criteria
Idiopathic Parkinson’s disease diagnosed by a neurologist	Medication:
	• Beta-blockers and/or anti-psychotics
Hoehn & Yahr stage ≤2 (tested in *off state*)	Comorbidity:
	• Neurologic or orthopedic co-morbidities that make it impossible to cycle or perform stretching exercises (safely)
	• Contra-indications for aerobic exercise including diagnosed cardiac diseases, diagnosed but poorly controlled diabetes
	• mellitus or pulmonary diseases.
	• Psychiatric diseases: major depressive disorder, severe or moderate depressive episode or any form of psychosis), diagnosed by a psychiatrist in the last year.
	• Dementia: MMSE <24
Age 30–75 years	Inability to fill out questionnaires or perform a computer task (i.e. due to poor vision, inability to read Dutch (illiteracy or foreign language))
Sedentary lifestyle [16]	Facilities:
	• No internet at home
Parkinson medication:	Availability/compliance:
• Stable dopaminergic medication dose (both levodopa and/or a dopamine agonist are allowed) for at least one month before the study	• Unavailable for more than 10% (approximately 2.5 weeks) of the 6 months
• No treatment and deemed unlikely to start treatment within the next month by their treating neurologist	

### Recruitment and setting

Participants will be recruited primarily through the neurology department at the Radboud university medical center (Radboudumc), Nijmegen, the Netherlands. Additional centers in the vicinity of Nijmegen will be invited to assist in the recruitment. The inclusion period will last 2.5 years. Eligibility is established through telephone screening and in-person assessments. During the telephone screening a trained research nurse interviews the patients regarding their physical activity (LAPAQ outdoor and norms of the ACSM [16]), comorbidity, medication use, ability to complete questionnaires or perform computer tasks, facilities at home and availability. If there is no reason for exclusion at this stage, participants are invited to the study site for in-person assessments. In-person assessments take place in the Radboudumc and include: (a) screening of cognitive function and disease stage (Hoehn & Yahr) without dopaminergic medication by a trained research nurse, (b) medical screening by a cardiologist to rule out any medical conditions that preclude endurance exercise; and (c) a maximal-graded exercise test to determine the presence of serious arrhythmias, evidence of ischemia or increases of diastolic blood pressure above 115 mmHg or increases of systolic blood pressure above 235 mmHg. Abnormalities observed during the graded exercise test require follow-up by a cardiologist to determine whether high-intensity exercise can be performed safely. Informed consent is signed at the beginning of the in-person assessments. If no exclusion criteria are met during the in-person assessments, patients are included and baseline measurements are performed.

### Randomization and blinding

Within two weeks after informed consent is signed, participants will be randomly assigned to one of the two groups using a web-based system designed by an independent statistician. The allocation ratio is 1:1 and the procedure entails permuted blocks of varying sizes (unknown to the study personnel). Minimization is performed for gender and medication status (treated/untreated). The patients, all study personnel involved in the screening and assessments and the researcher who will analyze the data will be blinded for the allocation. Randomization is performed by a member of the research team who is not involved in the assessments or the data analysis. Patients will be informed of their allocation after randomization by the coach (see below) but are unaware of the details of the two allocation possibilities. Blinding of patients will be checked after the patient has finished his/her participation by asking them whether they felt their prescribed program was effective.

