**Table 2 Tab2:** **Study schedule and assessments**

	t = wk 0	t = wk 1-2	t = wk 2-3	t = wk 26-27	t = wk 27-28
Activity/Assessment	Pre-study screening (phone)	Study visit 1 (Screening/Baseline)	@ home	Study visit 2 (post-intervention)	@ home

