Several studies in non-PD populations indicated beneficial effects of aerobic exercise on mood [40,41], sleep [42], constipation [43] and fatigue [44]; all of which are part of the non-motor symptoms that PD patients may experience. We will use self-rating questionnaires that are completed at home to assess these non-motor symptoms. Mood will be assessed with the Hamilton Anxiety and Depression Scale (HADS). This is a 14-item scale assessing both depression and anxiety and has been validated in PD patients [45]. The section on sleep of the Scales for Outcomes in Parkinson’s disease (SCOPA-Sleep) will be used to measure sleep disturbances. This a short practical self-rating scale designed to evaluate sleep quality and daytime sleepiness [46]. Autonomic symptoms can be assessed with the SCOPA-autonomic (SCOPA-AUT) [47]. For the purpose of this trial only the gastro-intestinal section of the SCOPA-AUT will be used to assess constipation. Fatigue will be addressed by the Fatigue Severity Scale (FSS), which has been recommended for screening and severity rating in PD by the movement disorders society [48].

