##### Quality of life

Quality of life will be assessed with the 39-item Parkinson Disease Questionnaire (PDQ-39), a PD specific self-administered questionnaire [49]. Participants are asked to fill out this questionnaire at home.

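### The schedule allows the baseline home questionnaires for five secondary outcomes to be answered after randomisation, so their ANCOVA baseline covariate may be a post-allocation value

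*Protocol article*

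**What the plan says.** Four parts of the article bear on the order of events.

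- **Consent.** Recruitment and setting: "Informed consent is signed at the beginning of the in-person assessments". In Table 2 these assessments are study visit 1.
- **Randomisation and disclosure.** Randomization and blinding: "Within two weeks after informed consent is signed, participants will be randomly assigned to one of the two groups", and then "Patients will be informed of their allocation after randomization by the coach (see below) but are unaware of the details of the two allocation possibilities".
- **Questionnaires.** Table 2 has the time columns "t = wk 0 t = wk 1-2 t = wk 2-3 t = wk 26-27 t = wk 27-28". From the second column on, they are labelled "Study visit 1 (Screening/Baseline) @ home Study visit 2 (post-intervention) @ home". The baseline marks for SCOPA-sleep, HADS, SCOPA-AUT, FSS and PDQ-39 are all in the home column at weeks 2-3; none is at visit 1. The text agrees. For the non-motor scales it says "We will use self-rating questionnaires that are completed at home to assess these non-motor symptoms", and for the PDQ-39 "Participants are asked to fill out this questionnaire at home".
- **Analysis.** The Statistical analysis plan section applies ANCOVA to every primary and secondary outcome, with the baseline value as a covariate.

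Recruitment and setting adds only that baseline measurements follow inclusion. It does not say that they must be finished before allocation.

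**The concern.** ANCOVA on a baseline value is unbiased in a randomised trial because the covariate cannot depend on the arm. A covariate recorded after the patient has been allocated, told the programme by the coach and perhaps started training no longer has that guarantee. If the arms already differ on it, the adjustment subtracts part of that difference from the estimated effect.

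The five scales make up the whole quality-of-life domain and all the non-motor symptom scales completed at home. Self-ratings are also the outcomes most open to expectation, which the design tries to control by withholding details of the other arm.

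**Working it through.** The plan gives no figure of its own on this point. The check sets the stated windows against each other and then sizes the possible bias.

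**1. Do the windows overlap?** Let visit 1 be at week v, with v between 1 and 2 (Table 2). Randomisation may fall in [v, v + 2]. The questionnaires are due in [2, 3].

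| Visit 1 | Permitted randomisation | Questionnaires | Overlap |
|---|---|---|---|
| week 1 | weeks 1-3 | weeks 2-3 | weeks 2-3 |
| week 1.5 | weeks 1.5-3.5 | weeks 2-3 | weeks 2-3 |
| week 2 | weeks 2-4 | weeks 2-3 | weeks 2-3 |

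The randomisation window covers the whole questionnaire window in every case, so either order is allowed.

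**2. When does the programme start?** The intervention lasts 6 months (Interventions), and follow-up comes directly after it (Study design), at weeks 26-27 (Table 2). Counting back:

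- 26 weeks: start in weeks 0-1
- 25 weeks: start in weeks 1-2
- 24 weeks: start in weeks 2-3

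A start after week 3 would leave less than 27 - 3 = 24 weeks. The schedule therefore leaves little room for training to begin only after the questionnaire window. The 26-week result falls before or at the earliest visit 1, so the columns are clearly rounded and this step is indicative only.

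**3. How often could the order be reversed?** The documents do not say. As an illustration, suppose v is uniform on weeks 1-2, the questionnaire date is uniform on weeks 2-3, and randomisation is uniform on the m weeks after visit 1, all independent. Let T be the questionnaire date minus v, which is triangular on 0-2 weeks with mean 1. The share of questionnaires that follow randomisation is E[min(T, m)]/m:

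- m = 2: 1/2 = 50%
- m = 1: 1/3 + 1/2 = 83%
- m = 0.5: (0.0417 + 0.4375)/0.5 = 96%

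The verdict does not rest on these shares.

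**4. How large could the bias be?** Let D be the true between-arm difference at follow-up, f the fraction of D already present on average in the recorded baseline, and b the ANCOVA slope on baseline. Then

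estimate = D - b × (f × D) = D × (1 - b × f).

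| b | f = 0.05 | f = 0.10 | f = 0.25 |
|---|---|---|---|
| 0.5 | 97.5% | 95.0% | 87.5% |
| 0.7 | 96.5% | 93.0% | 82.5% |
| 0.9 | 95.5% | 91.0% | 77.5% |

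Entries are the estimate as a share of the true effect. Both b and f are assumptions. The pilot value of 0.7 in the Power and sample size section is a correlation for the motor score, not a slope for any of these questionnaires. Because f averages over all patients, it shrinks if only some of them answer after allocation.

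**5. What is outside the problem?** Table 2 schedules MDS-UPDRS III off (the primary outcome) and the other visit-based measures, including MDS-UPDRS IV and falls, at visit 1. The sample size calculation concerns the primary outcome and is not touched.

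**The case against.** The strongest reply is that this argues from silence in a condensed article. The order of questionnaire return, release of allocation and coach contact is operational detail. The standard operating procedures and the study-design figure are not shown and may fix it. The two-week allowance also leaves room for the questionnaires to come first, and that may well be the intention. This stands to a point: the reversed order is permitted, not stated to occur. But the article does publish the windows, they overlap completely, and its follow-up timing favours an early programme start. That is more than a detail left out.

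The second reply concerns expectation. Disappointment in one arm and enthusiasm in the other largely presuppose that patients know what they did not get, and the article says they do not know the details. This stands: differential expectation is reduced. It does not remove reactions to the patient's own programme, or early effects of training.

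The third reply is that allocation, disclosure and first training are separate steps, and none is dated before the questionnaires. The control programme needs a home visit by the coach, and cycling needs equipment in the home. This also stands, and it limits how much exposure could precede the answers.

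A reader might infer that 50-80% of the treatment effect is lost, from slopes of 0.5-0.8. The documents do not support that. Such a percentage applies to the early shift only, and the size of that shift is unknown.

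**Conclusion.** The point holds in a limited form. As scheduled, the five home questionnaires may be completed after allocation, and the ANCOVA would then treat a post-randomisation value as baseline. The likely effect is modest: the estimate is about 78-98% of the true effect for f of 5-25% and b of 0.5-0.9, both assumed. If early change goes the same way as the final effect, the bias is towards no difference. A reaction to the assigned programme could push it either way.

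A reader might go further and infer that these baselines are in fact taken after allocation, or that the randomised comparison is broken for patient-reported outcomes. Neither follows from an order that is merely allowed, with at most about two weeks of exposure. Only secondary outcomes are involved. The change is still worth making, because it is nearly free and removes the question altogether.

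**What to change.** - **Order.** State that the baseline home questionnaires precede randomisation, and have the web-based system release an allocation only when all five are time-stamped as complete. They are e-mailed and imported into the database on completion (Data collection and management), so the check is practical. Weeks 2-3 lie within two weeks of consent for a visit 1 at week 1 (limit week 3) or week 2 (limit week 4).
- **Dates.** Record the completion date of each questionnaire and the dates of randomisation and of the coach's disclosure.
- **Analysis.** Treat any questionnaire completed after allocation as a missing baseline, imputed from pre-randomisation data without using the arm (the overall baseline mean, or a regression on visit-1 variables). At the least, run a sensitivity analysis that does not use such values as observed.
- **Schedule.** Reconcile the weeks in Table 2 with the stated intervention length, since the two do not fit exactly.

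The cost is one hard check in the randomisation form, an e-mail reminder, and a few days' delay for slow responders within the existing window. The sample size does not change. If practice already follows this order, one added sentence settles the matter.

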### Measurements

Assessments will be performed at baseline and after 6 months. All measurements are only performed in *off* state, except for the maximal graded exercise test which is performed in the *on* state and in the UPDRS III, which is performed in both the *off* state (primary outcome) and in the *on* state (secondary outcome). The maximal-graded exercise test is performed in *on* state for two reasons: 1) to minimize any PD related motor limitations, allowing for a maximal cardiovascular performance, and 2) because patients are also instructed to train during their participation in the study in their optimal therapeutic state (*on* state) and the training intensity will be based on the maximal heart rate determined in the maximal graded exercise test. *Off* state is determined as >12 hours after the last Parkinson medication intake (and if applicable: deep brain stimulation switched off during the measurements). Therefore all patients are asked to skip the morning dose of their Parkinson medication at the day of the assessment. All assessments will start at the same time of the day and will be performed in the same sequence, minimizing the difference in time spent in the *off* state between participants. At the end of the assessment, the two aforementioned tests are performed in the *on* state. *On* state is determined by 1 hour after taking a supra-threshold dose of their morning medication (125% of their morning levodopa equivalent dose (LED) for levodopa [19,20]). Half an hour before their lunch, patients are instructed to take this supra-threshold dose to ensure that they reach an *on* state that is equivalent to their everyday functioning, and that persists throughout the *on* state assessments. All tests and questionnaires used are described in Table 2 and are detailed here below.

